**Trial Stopping Guidelines**

The DSMB has the responsibility for deciding whether the trial should be stopped at any stage. They will do this if, and only if, two conditions are satisfied:

1. The results provide proof beyond reasonable doubt that the intervention is on balance definitely harmful, or for a particular category of, participants in terms of the major outcome; or is on balance, definitely having a therapeutic effect (noting that this is extremely difficult to assess without long-term follow-up periods).
2. The TSG are not conducting the project safely, which would include, but is not limited to, a failure to contact participants who flag as ‘at risk’ (scores >20 on the SIDAS) within the 48 hour period specified in the Duty of Care section within the Trial Protocol.

There is no plan to conduct any interim analyses, unless in cases where there is justification to unblind the data and condition (1) above is met. If this occurs, this DSMB Charter is in agreement with the Peto-Haybittle stopping rule whereby an interim analysis of a major endpoint would generally need to involve a difference between treatment and control of at least three standard errors to justify premature disclosure. An interim subgroup analysis would have to be even more extreme to justify disclosure. This rule has the advantage that the exact number and timing of interim analyses need not be pre-specified. In summary, the stopping rules require extreme differences to justify premature disclosure and involve an appropriate combination of mathematical stopping rules and scientific judgment.

#

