# Outcomes and Schedule of Surveys

## 6.1. Primary outcome measure

**Suicidal Ideation Attributes Scale**

The primary outcome measure is the severity of suicidal thoughts assessed by the Suicidal Ideation Attributes Scale (SIDAS; van Spijker, Batterham [23]). It consists of five questions pertaining to frequency of suicidal thoughts in the past month, controllability of suicidal thoughts, closeness to suicide attempt, level of distress associated with the thoughts, and impact on daily functioning. Each item is assessed on a 11-point scale (0-10). Item two (controllability) is reverse scored. Total scale scores on the SIDAS range from 0 to 50, with higher scores indicating more severe suicidal thoughts.

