## 6.2. Secondary outcome measures

**Suicide Behaviours**

Participants’ previous suicide attempts and self-injury are assessed by eight questions developed for a previous suicide prevention trial [23]. Participants are invited to indicate whether they have attempted suicide in their lifetime and in the past 30 days on a three-point Likert scale, ranging from ‘No, never (0)’, ‘Yes, once (1)’, to ‘Yes, more than once (2)’. They are also asked to report the number of suicide attempts over their lifetime, and the number of months that they have been thinking about suicide. Apart from that, participants are asked to indicate whether they have intentional self-injury in their lifetime on the aforementioned three-point Likert scale. If yes, they are asked to provide the number of times of their intentional self-injury and rate the severity of the worst injury in the past month on a three-point Likert scale, ranging from ‘No care was needed (1)’, ‘Some care was needed (2)’, to ‘Required medical care (3)’.

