**Suicidal Ideation Attributes Scale (SIDAS)**

**Now we’re going to ask you some questions are about your suicidal thoughts, and the severity of them.**

**Please think about the past month when answering the following questions.**

##

| In the past month, how often have you had thoughts about suicide? | | | | | | | | | | |
| --- | --- | --- | --- | --- | --- | --- | --- | --- | --- | --- |
| 0  Never | 1 | 2 | 3 | 4 | 5 | 6 | 7 | 8 | 9 | 10  Always |
| In the past month, how much control have you had over these thoughts? | | | | | | | | | | |
| 0  No control | 1 | 2 | 3 | 4 | 5 | 6 | 7 | 8 | 9 | 10  Full control |
| In the past month, how close have you come to making a suicide attempt? | | | | | | | | | | |
| 0  Not close | 1 | 2 | 3 | 4 | 5 | 6 | 7 | 8 | 9 | 10  Made an attempt |
| In the past month, to what extent have you felt tormented by thoughts about suicide? | | | | | | | | | | |
| 0  Not at all | 1 | 2 | 3 | 4 | 5 | 6 | 7 | 8 | 9 | 10  Extremely |
| In the past month, how much have thoughts about suicide interfered with your ability to carry out daily activities, such as work, household tasks or social activities? | | | | | | | | | | |
| 0  Not at all | 1 | 2 | 3 | 4 | 5 | 6 | 7 | 8 | 9 | 10  Extremely |

**We’d just like to ask you a few more questions about prior self-harm behaviour. Just to remind you, these questions are completely voluntary.**

| **What the user will see** | | **Drop down response options available** |
| --- | --- | --- |
| Have you ever attempted suicide? | --- select ---- | No, never Yes, once  Yes, more than once |
| If more than once, how many times? | --- select ---- | 2  3  4  5  6+ |
| How many months have you been thinking about suicide? | --- select ---- | 1 or less  2  3 to 6  >6 to 12  >12 to 24  >24 to 36  >36 |
| How often, on average, do you think about suicide? | --- select ---- | Daily Weekly Monthly  Less than monthly |
| Have you attempted suicide in the past 30 days? | --- select ---- | No, never Yes, once  Yes, more than once |
| Have you ever injured yourself on purpose (i.e., intentional, self-inflicted damage to the surface of the body without suicidal intent) | --- select ---- | No, never  Yes, once  Yes, more than once |
| In the past month, how often have you injured yourself on purpose? | - If ‘Yes, more than once’ then select - | 2-5 times (low)  6-9 times (moderate)  10-20 times (high)  20+ times (severe) |

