**DSMB Meetings**

The first meeting

The members should review this charter and form an understanding of the protocol and study endpoints. Meetings will take place at an appropriate regularity decided by the DSMB committee. The DSMB will also meet if evidence from other research groups suggests potential for risk.

Meeting formats

DSMB meetings will be booked in for the week following the completion of data collection at each assessment point of the trial (baseline, post-intervention, 3-month post-intervention follow-up). Procedurally, when these set meetings are booked they will include both an open and closed session, however, it is up to the DSMB to decide if they would like to have a closed session. The typical structure of the meetings will first start with an open session involving both DSMB members, the trial leads, and the trial manager, followed by the closed session if needed. The meetings will be organised and chaired by either MT or JH. These meetings will generally be conducted by teleconference or videoconference, but the DSMB can decide whether they would like to do this face-to-face.

In the event of a closed meeting, unblinded data may be requested if there is a rationale (e.g. unexpected adverse events, aggregate data indicates self-harm above the rates expected from this group). Only DSMB members and others whom they specifically invite are present in closed meetings.

Outside of the pre-scheduled meetings, an extraordinary meeting may be called if a serious adverse event occurs. The trial leads or trial manager will report the event to the Chair within 24 hours of becoming aware of the event, and the Chair will convene a closed session meeting to discuss the event and make recommendations.

Following each meeting, a report minuting the open session including any DSMB recommendations and rationale for such will be prepared by the minute taker and sent to the CIA (MT) and all other members. For closed sessions, recommendations will be prepared by the Chair and sent to the Trial Lead (MT), who will present the outcomes at the TSG following each meeting. Meetings will occur until the trial concludes.

Reporting

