**Safety Analyses**

Safety analyses are:

- Suicidal ideation, as measured by:
- % scoring >20 on the SIDAS
- A recent suicide attempt (identified at post-intervention or follow up survey via Q “Have you attempted suicide in the past 30 days?’ or ad hoc self report by participants to research study email)
- Serious adverse events (including all hospitalisations and deaths).
- Enrollment data, intervention completion data, attrition data, adverse event data, and other administrative data.

The TSG cannot access the unblinded data for suicidal ideation or attempt as these are outcome measures and will be shared only in a closed session.

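### The DSMB stopping guideline ties harm to an undefined major outcome and does not link the deaths and suicide attempts the DSMB reviews to that criterion

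*Protocol*

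**What the plan says.** The Trial Stopping Guidelines (Appendix E) give the DSMB responsibility for deciding whether to stop, and add: "They will do this if, and only if, two conditions are satisfied". Condition (1) sets a standard of proof beyond reasonable doubt, and its harm limb reads: "the intervention is on balance definitely harmful, or for a particular category of, participants in terms of the major outcome". The other limb of that condition is a definite therapeutic effect. Condition (2) is about conduct: "The TSG are not conducting the project safely". The same section allows an interim analysis only where unblinding is justified and condition (1) is met, and says that a difference of at least three standard errors on a major endpoint would generally be needed.

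The charter does not define the major outcome. Section 6.1 says: "The primary outcome measure is the severity of suicidal thoughts assessed by the Suicidal Ideation Attributes Scale". Section 7 and the charter's first objective also name SIDAS. Attempts come under secondary measures in Section 6.2: "Participants’ previous suicide attempts and self-injury are assessed by eight questions developed for a previous suicide prevention trial".

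Other passages treat clinical events as central to safety:

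- Safety Analyses (Appendix E) lists the percentage above 20 on SIDAS, recent suicide attempts, and an entry that opens with "Serious adverse events (including all hospitalisations and deaths".
- DSMB Meetings lets the board request unblinded data if, for example, "aggregate data indicates self-harm above the rates expected from this group".
- The charter's list of DSMB duties includes recommending that the trial continue, be modified or be terminated, with no restriction by outcome.
- Section 12.1 lets the board recommend a pause or discontinuation on account of risk issues or adverse events.

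**The concern.** The section that governs stopping is worded as exclusive, and its harm limb names one outcome in the singular. The natural reading of that outcome is SIDAS. The events that matter most in a trial of young people with suicidal ideation are reviewed by the board but have no stated route to the harm criterion. Unblinding for excess self-harm leads back to a condition that does not mention self-harm.

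At stake is clarity when it is most needed. If deaths or attempts accumulated in one arm while mean ideation stayed level, the board would hold two mandates that do not agree: a wide power to recommend termination, and a stopping guideline confined to the major outcome.

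**Working it through.** **Passages side by side.** Three readings of the major outcome can be tried.

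1. SIDAS only: attempts count only through their effect on the scale, and deaths do not count.
2. SIDAS and attempts: deaths and other serious adverse events still do not count, because Safety Analyses lists them separately.
3. All listed safety outcomes: nothing in the stopping guideline says this.

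On none of these does the stated text tie deaths to harm.

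**Number analysed.** Section 8 gives d = 0.30, pre-post correlation 0.50, attrition 30%, power 0.80 and alpha 0.05 (two-sided assumed).

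- n per arm = 2 × (1.960 + 0.842)² × (1 − 0.50²) / 0.30² = 131
- Inflated for attrition: 131 / 0.70 = 188, against 189 stated. The plan's figure reproduces.
- Completers: 189 × 0.70 = 132 per arm.

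**How far attempts move mean SIDAS.** SIDAS runs from 0 to 50. Item 3 asks "In the past month, how close have you come to making a suicide attempt" and scores 10 for an attempt made. The documents give no SIDAS SD, so 8 to 12 is assumed. A row at 5 is added because Section 4.1 restricts entry to scores below 21. The points that one attempt adds are also assumed: 10 if only item 3 moves, from 0 to 10, and 20 or 30 if other items rise too.

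- SE of the arm difference = SD × √(2/132), multiplied by √0.75 if adjusted for baseline. For SD 8 to 12 this is 0.85 to 1.48 points.
- Excess attempts needed for 3 SE = 3 × SE × 132 / points per attempt, rounded up.

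| SD | SE basis | 3 SE (points) | 10 points each | 20 each | 30 each |
|---|---|---|---|---|---|
| 5 | unadjusted | 1.85 | 25 | 13 | 9 |
| 5 | adjusted | 1.60 | 22 | 11 | 8 |
| 8 | unadjusted | 2.95 | 39 | 20 | 13 |
| 8 | adjusted | 2.56 | 34 | 17 | 12 |
| 10 | unadjusted | 3.69 | 49 | 25 | 17 |
| 10 | adjusted | 3.20 | 43 | 22 | 15 |
| 12 | unadjusted | 4.43 | 59 | 30 | 20 |
| 12 | adjusted | 3.84 | 51 | 26 | 17 |

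For example, eight excess attempts at 10 points each shift the arm mean by 80/132 = 0.61 points, which is 0.4 to 0.7 SE for SD 8 to 12.

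**Attempts compared directly**, 132 per arm, pooled z:

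- 8 v 0: z = 2.87
- 9 v 0: difference 9/132 = 0.0682; SE = √(0.0341 × 0.9659 × 2/132) = 0.0223; z = 3.05 (Fisher p = 0.0034)
- 10 v 0: z = 3.22 (Fisher p = 0.0016)
- 15 v 3: z = 2.93

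Three standard errors correspond to a two-sided p of 0.0027. The direct comparison crosses at about 9 v 0, or 10 v 0 by the exact test. It needs a larger excess when the other arm also has attempts.

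**Deaths.** A participant who dies has no later SIDAS score. Section 7 handles missing follow-up under a missing-at-random assumption, so a death adds no observed value at any count.

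**The case against.** The strongest reply is that the board is not powerless. A reader might infer from the stopping guideline that deaths and attempts cannot establish harm, or that the DSMB may not act on them. The documents do not support that. Section 12.1 and the charter's list of duties let it recommend discontinuing or terminating, a serious adverse event can trigger an extraordinary closed meeting, and the guideline itself combines mathematical rules with scientific judgment. What remains is a conflict between these passages and the exclusive wording of the guideline.

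A reader might also take it as settled that the major outcome is SIDAS. That is an inference. Safety Analyses calls both ideation and attempt outcome measures, and the closed session receives analyses of both. A reading that includes attempts is open, but it does not reach deaths.

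A third tempting reading is that falling mean ideation with rising attempts could satisfy the benefit limb. That limb demands a definite therapeutic effect on balance, proved beyond reasonable doubt, and a board seeing more attempts or deaths would hardly find it met.

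On the arithmetic, an attempt is not trivial for one person: 10 points is a fifth of the scale and half of the 20-point alert level. Other items cover the same month and may rise too, and the SIDAS safety measure is the percentage above 20, not the mean. At SD 5 and 30 points per attempt, mean SIDAS is about as sensitive as a direct comparison (8 to 9 attempts). The insensitivity therefore depends on the assumptions, except for deaths, where it does not.

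**Conclusion.** The concern holds as an inconsistency in a stated rule. The guideline restricts harm to an undefined major outcome and does not link to it the deaths, hospitalisations and attempts that the same charter makes safety analyses. It does not follow that these events go unmonitored or that the board could not respond.

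For SD 8 to 12, the excess attempts needed to move mean SIDAS by three standard errors are 34 to 59 at 10 points each. At 30 points each they are 13 to 20 unadjusted and 12 to 17 adjusted. These figures rest on an assumed SD, assumed points per attempt, 132 completers per arm and no other difference between arms. Three standard errors serve here as the charter's own yardstick, which it applies only generally.

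There is a linked ambiguity. Read literally, both conditions must be satisfied, so harm alone would not suffice unless the steering group were also conducting the trial unsafely. This should be fixed, but the wider powers elsewhere keep it short of a critical fault.

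**What to change.** Define the major outcome in the Trial Stopping Guidelines. Reconcile condition (1) with Section 12.1 and with the charter's DSMB duties, DSMB Meetings and Safety Analyses, so that the charter says the safety outcomes already reviewed (deaths, attempts, other serious adverse events and SIDAS) bear on a finding of harm, which is not limited to mean SIDAS. In the same edit, state whether conditions (1) and (2) must both hold or whether either is enough.

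How much evidence is needed on each outcome is for the sponsor and the DSMB to decide. A rule that any excess suffices would sit badly with the charter's standard of proof, and none is proposed here.

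The cost is a short charter amendment, agreed by the DSMB and consistent with Section 12.1. It needs no new data and no change to sample size or the primary analysis.

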**DSMB Documentation and Communication**

1. Available information at open sessions

This will include routine study information (consent, completion, attrition), risk alerts, follow-up data, by group.

1. Available information at closed sessions

Unblinded data for SIDAS and suicide attempt data and statistical analyses for this data (including effect size estimates).

1. Blinding

If necessary, the DSMB will be provided unblinded data by the data officer.

1. Access to unblinded data

Only the DSMB members, trial leads and the trial manager have access to this data. The DSMB cannot share this beyond the committee to the trial team.

1. Who is responsible for circulating external evidence (e.g., from other trials, population-based

prevalence estimates)?

Trial manager, [name].

1. To whom will the DSMB communicate decisions and recommendations?

Within two weeks following each meeting, the DSMB will send findings and recommendations to the Trial Steering Group (TSG), listed on p. 5.

1. How are responses communicated back to the DSMB?

The TSG (Co-chaired by MT or JH) will review and respond to the DSMB recommendations if required. If the recommendations request action, the PI will provide a written response stating whether the recommendations will be followed and the plan for addressing the issues. Upon receipt, the DSMB will consider the TSG response and will attempt to resolve relevant issues, resulting in a final decision. The investigator will agree to disseminate the final decision to the appropriate regulatory agencies (TGA and HREC) within an appropriate time.

1. What happens to the reports after each DSMB meeting?

All DSMB members are asked to destroy reports after each meeting. Internal records will be kept by the data manager. Each report will add a table onto the previous one, and as such the reports will be cumulative.

1. What happens to minutes and records?

Any minutes should be kept by the Chairs until after the final trial analysis is complete, upon which point they should be shared with the Trial Manager for archiving for a minimum of 7 years.

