# Study Design

## 3.1. Treatment Design

The flowchart (Figure 1) summarizes this study which will consist of evaluating the efficacy of a digital therapeutic for suicidal ideation, using a is a two-arm, parallel, double-blind superiority randomised controlled trial design. Following completion of the baseline (T0) assessment, participants will be randomised at equal allocation (2:2) to one of two smartphone applications, a DBT-based application (LifeBuoy) or a placebo (non-therapeutic) control application (LifeBuoy-C). After completion of the 6 week intervention, primary, secondary and tertiary outcomes will be assessed at immediate post-intervention (T1) and then at 4-months post-intervention (T2). All surveys will be completed online, with survey links distributed automatically to registered participants using Black Dog Institute’s research engine. Subjects in the intervention condition will be invited to participate in a qualitative intervention at the final assessment to understand their experience with the LifeBuoy application.

[figure not shown]

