## 4.2. Study Recruitment Procedures

**Trial.** Participants will be recruited into this trial via social media advertisements (e.g. Facebook, Twitter, Instagram, website), which are targeted to the inclusion criteria. Individuals interested in participating will click on the following link, which will be embedded in the advertisements:

https://blackdoginstitute.org.au/lifebuoy_study.

This link will take participants through to the study website hosted on Black Dog Institute’s research engine. Here they will be presented with an online version of the participant information sheet and consent form. Participants will need to consent to participation before being directed on to the eligibility screening survey. This strategy has been successfully used in a recent trial of a relationship app for depression, and 399 eligible participants were recruited and registered in one month. 71 (17.7%) of those recruited completed baseline assessments, indicating that the required sample size for this trial will take six months.

Recruitment wording in described in Appendix A.

**Qualitative Interviews.** For the qualitative interviews conducted at the final (T2) assessment, we will recruit a 10% subsample of individuals who participated in the intervention condition (expected to recruit n=189) to assess their experience with the app. Justification for this sample size is described in Section 8.

Recruitment to the qualitive interviews will take place immediately *before* the final assessment. At the time of the final assessment, but prior to receiving the assessment, participants in the intervention group will be emailed a letter of invitation to participate in the qualitative study, using the details they registered for the trial with. The delivery of this invite will be automated as part of a pre-determined schedule of survey and reminder delivery in the Research Engine.

The wording for the letter of invitation is as follows:

**“Before you start the final assessment, we just want to check if would you be interested in participating in a 30-minute one-on-one telephone or videoconference interview about your experience of using the LifeBuoy app? We are keen to hear from you if you did or did not use the app, to learn why. You will be reimbursed $30 for your time if you chose to participate:**

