## 4.4. Condition Allocation

After screening and registration is complete, participants will be asked to complete the baseline assessment – which is also delivered online, via the trial portal (website). Upon completion of the baseline survey, they will be automatedly randomised to a condition via an algorithm built into the Research Engine trial software. Subjects are not informed of which condition they have been allocated to. The two applications both have LifeBuoy in their title and look the same, only the content differs.

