In terms of expedited reporting of events to the DSMB in between its regular sessions, the process will be guided by the NHMRC ‘Risk-based Management and Monitoring of Clinical Trials Involving Therapeutic Goods, 2018’, bearing in mind that this is a trial of an mhealth preventive intervention and not a medicine or treatment. The trial is regarded as being in the lowest risk category, type A, with risk comparable to standard medical care. All Serious Adverse Events (SAEs) will be regarded as non-expedited (ie. only to be reported at the next DSMB meeting), unless the SAE is both unexpected and possibly related directly to participation in the trial, in which case it will be reported to the DSMB via email within 24 hours as well as other agencies. For this 6-week low intensity app-based DBT intervention, it is anticipated that all SAEs that are possibly related to trial participation will be reported. In the event of uncertainty, the TSG should default to reporting the SAE to the DSMB.

Responsibilities of the Data Officer

The data officer will be responsible for producing the closed session report to the DSMB, and assist the trial manager with the open session report. The main purpose of this role is to ensure that the Investigator team remain blind to study outcome data. No interim analyses will be performed unless explitly required by the DSMB with a strong rational. The process for communicating the report is as follow:

- The data officer will extract unblinded data and prepare reports for the DSMB (using the attached shell) and disseminate the report one week prior to the scheduled meeting.
- The data officer will be responsible for extracting both confidential and non-confidential data from the trial data collection platform.
- The data officer will participate in the DSMB meetings to take the members through the report if required.
- These discussions will remain confidential and not communicated to the trial team.

Responsibilities of the Chief Investigator and Trial Streering Group (TSG)

- The trial leads and trial manager must be available to attend open sessions.
- Other TSG members (see membership details on p. 5) are not required to attend, but may attend if they wish to.

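### The DSMB charter both grants and denies trial leads access to unblinded primary-outcome data; separately, only the intervention arm is contacted just before T2

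*Protocol*

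**What the plan says.** The trial is described in section 3.1 as a "two-arm, parallel, double-blind superiority randomised controlled trial design", and section 4.4 adds: "Subjects are not informed of which condition they have been allocated to".

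**Unblinded outcome data.** The charter section DSMB Documentation and Communication lists the closed-session material as SIDAS and suicide attempt data by arm, with analyses and effect size estimates. Its item on access reads: "Only the DSMB members, trial leads and the trial manager have access to this data". The sentence after it forbids the DSMB to pass the data to the trial team. Under Safety Analyses: "The TSG cannot access the unblinded data for suicidal ideation or attempt as these are outcome measures". The duties of the data officer are meant to "ensure that the Investigator team remain blind to study outcome data".

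**Open sessions.** Meetings start with "an open session involving both DSMB members, the trial leads, and the trial manager". On the content of these sessions: "This will include routine study information (consent, completion, attrition), risk alerts, follow-up data, by group".

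**Interview invitation.** Section 4.2 states that, at the time of the final assessment but before the survey is received, "participants in the intervention group will be emailed a letter of invitation to participate in the qualitative study". Those who say yes read an information sheet and give consent before going on to T2. Those who say no go straight to the survey.

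**The concern.** A charter that both permits and forbids the same access does not protect the blind, because a trial lead who looked at the SIDAS results by arm could point to a sentence that allows it. SIDAS is self-reported online, so the risk is not biased rating. It lies in decisions on conduct and analysis taken by people who already know the T1 result. Such knowledge cannot be withdrawn once given.

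The open-session content is a weaker route to the same end. Alerts split by arm can hint at the direction of the effect even when SIDAS means are withheld.

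The invitation is a different matter. One arm receives an extra message, with a paid interview on offer, immediately before a SIDAS measurement that belongs to the primary aim. The control arm receives nothing comparable. This could alter who answers T2, or how, in one arm only.

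**Working it through.** **1. Access: the charter statements side by side.**

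| Charter section | Trial leads and trial manager may see unblinded SIDAS? |
|---|---|
| DSMB Documentation and Communication, access item | Yes, both are named |
| Same item, next sentence | No, not to be shared with the trial team |
| Safety Analyses, with TSG membership under Reporting | No, the TSG is barred and they are members |
| DSMB Meetings, data officer duties | No, the role exists to keep investigators blind |
| DSMB Meetings, closed sessions | No, unless the DSMB specifically invites them |

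One statement grants access and four deny or restrict it. The granting sentence also leaves out the data officer, who extracts the unblinded data.

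**2. Timing.** Meetings are booked for the week after data collection ends at each assessment point. H1 is tested at post-intervention (T1). A T1 effect estimate could therefore reach the leads while T2 is still outstanding.

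**3. What by-group alerts could show (illustration).** Section 8 gives d = 0.30, attrition 30%, pre-post correlation 0.50 and 189 per arm. Its sample size reproduces with baseline adjustment and two-sided alpha 0.05 (sidedness is not stated):

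- n = 2 × (1.960 + 0.842)² × (1 − 0.50²) / 0.30² = 130.8, so 131 completers per arm
- 131 / 0.70 = 187.1, so 188 per arm, against 189 stated
- completers at 189 per arm: 189 × 0.70 = 132.3

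The alert rate is not in the documents, so a range is assumed. Suppose that an alert means SIDAS above 20, that scores are normal, that the true effect is 0.30 SD, and that 132 per arm are observed. If the control rate is p, the intervention rate is 1 − Φ(z + 0.30), where z is the normal quantile at 1 − p. For p = 30%, z = 0.524 and 1 − Φ(0.824) = 20.5%.

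| Assumed control rate | Expected alerts, control vs intervention | Difference / SE | Chance control count is higher |
|---|---|---|---|
| 10% | 13.2 vs 7.5 | 1.3 | 88% |
| 20% | 26.4 vs 16.7 | 1.6 | 94% |
| 30% | 39.6 vs 27.0 | 1.8 | 96% |
| 40% | 52.8 vs 38.3 | 1.9 | 97% |

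The direction would usually be visible, but the expected difference stays below two standard errors throughout. It is a hint, not a result.

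**4. The one-arm contact before T2 (illustration).** The documents give no size for any reporting shift. Carrying the section 8 assumptions over to T2, the standard error of the adjusted difference is √0.75 × √(2/132.3) = 0.106 SD. If there were no true effect and the contact shifted T2 SIDAS by b in one arm, the chance of a significant T2 difference would be:

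| Assumed b (SD) | b / SE | Chance of p < 0.05 |
|---|---|---|
| 0 | 0 | 5.0% |
| 0.05 | 0.47 | 7.6% |
| 0.10 | 0.94 | 15.6% |
| 0.20 | 1.88 | 46.8% |

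Nothing in the documents shows which of these values, if any, would apply.

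**The case against.** The strongest reply on access is that a single sentence is out of line with the rest of the charter, and that the intention to keep investigators blind is plain. Closed sessions are optional, unblinded data may be requested only with a rationale, and no interim analysis is planned. Randomisation, assessment and study procedures are automated, so leads have little opportunity to influence outcome measurement. All of this stands. It shows that the charter is inconsistent rather than designed to unblind. It does not remove the sentence, which is the one a reader would consult to learn who may see the data.

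On open sessions, risk alerts are not defined as SIDAS above 20 alone. Section 12.1 also describes a help button and a week-3 safety check, so alerts may include events that are not T1 or T2 outcomes. Follow-up data could mean completion only, and group labels could be coded. If the SIDAS < 21 entry criterion is applied, a simple normal shift is also doubtful. These points reduce the item to an ambiguity with a possible leak, and the alert table must be read in that light.

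On the invitation, the wording refers to the LifeBuoy app, a name that both apps carry, and identifies no arm. The payment is for the interview, not for T2. The information sheet and consent form reach only those who answer yes. H1 and the sample size concern T1, which is measured earlier. All of this stands. What remains is unequal contact before T2.

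**Conclusion.** The charter contradicts itself on who may see unblinded SIDAS and attempt data, and one of its statements is wrong if the trial is to stay blind to its investigators. This rests on the text alone and needs no assumption. It should be corrected before any closed-session report is produced. The by-group content of open sessions is a secondary route. Under the assumptions shown it would usually reveal the direction of effect, but with limited certainty.

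The invitation order is a separate point of lower severity. It concerns T2 only, and the size of any effect is unknown.

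A reader might infer that the plan as a whole breaks its own double blind, that grouped alerts disclose the primary outcome, or that the invitation tells participants their allocation. The documents support none of these. Most of the charter forbids the access, alerts are not defined as the primary outcome, and the invitation text names no arm.

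**What to change.** - **Charter, access item:** name only the DSMB members and the data officer as having access to unblinded data, and remove the trial leads and trial manager. This brings the item into line with Safety Analyses and DSMB Meetings.
- **Charter, open sessions:** present risk alerts and follow-up data pooled over arms, and keep the split by arm for closed sessions.
- **Section 4.2 (lower priority):** show the interview invitation only after T2 has been submitted.

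The first two changes are wording. The third reorders one automated message, and its only cost is slightly later interview recruitment.
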